## Abstract

**Background:**

Posttraumatic stress disorder (PTSD) rarely remits over time, and if left untreated, leads to significant distress, functional impairment, and increased health care costs. Fortunately, effective evidence-based treatments (EBTs) for PTSD, such as Prolonged Exposure (PE), exist. Despite their availability and efficacy, a significant number of individuals with PTSD do not initiate treatment when offered or dropout prematurely. One proposed theory suggests that the emotional-numbing symptoms of PTSD (e.g., blunted affect, apathy) can serve as a barrier to engaging in, and successfully completing, treatment; and the broad human-animal interaction (HAI) literature available suggests that HAI can potentially reduce emotional numbing related to PTSD. Accordingly, this manuscript describes an ongoing, federally funded, randomized controlled trial testing the efficacy of RESCUE, an HAI intervention, as a viable adjunctive treatment component for PE.

**Methods/design:**

The study will include 70 veterans with PTSD treated at a Southeastern Veterans Affairs Medical Center (VAMC). All participants in the trial receive up to 12 sessions of PE. Participants are randomly assigned 1:1 to (1) volunteer at a local animal shelter or (2) volunteer at a community agency of their choice as part of their in-vivo exposure exercises for PE. Outcomes will be examined via standard clinical interviews, self-report questionnaires, and thematic interviews.

**Discussion:**

It is hypothesized that participants in the HAI condition will report greater decreases in emotional-numbing symptoms and increased treatment compliance and completion rates relative to those in the community volunteer condition. If successful, RESCUE, could be easily incorporated into standard PE and broadly disseminated.

**Trial registration:**

ClinicalTrials.gov. ID: NCT03504722. Retrospectively registered on 2 May 2017.

## Background

Prolonged Exposure (PE) is considered an evidence-based treatment (EBT) for PTSD [1, 2] and has been widely disseminated throughout Department of Defense (DoD) and Veterans Affairs (VA) treatment facilities. Although up to 80% of patients demonstrate clinically meaningful improvement after completing an EBT for PTSD such as PE [1–3], a significant number of individuals do not initiate PTSD treatment or drop out of treatment prematurely (as high as 78% and 36% overall pooled dropout rates across studies) [4–7]. Given the wide-scale availability of PE and other EBTs for PTSD in VA and DoD treatment settings, and the robust effect sizes for treatment completers, there is a need for novel methods that can improve PTSD treatment engagement and decrease attrition.

One potential avenue for improving EBTs for PTSD is by targeting PTSD symptoms that may adversely impact treatment engagement early in the treatment process. Emotional numbing is part of the symptom profile of PTSD and consists of symptoms that reflect difficulties in experiencing positive emotions such as love and happiness, loss of interest in activities that were previously important or pleasurable, and feeling distant and cut off from others. In relation to PTSD and other psychiatric disorders, emotional numbing is also associated with apathy and low motivation [8, 9]. Together, these symptoms can limit an individual’s ability and willingness to engage in treatment [10, 11], particularly a treatment that encourages connecting emotionally with trauma-related material. Consistent with this, poor response to PE has been associated with blunted emotional reactivity to trauma cues early in therapy [12].

A promising mechanism for decreasing emotional numbing is through therapeutic human-animal interaction (HAI [13–15]). HAI refers to the purposeful and semistructured social pairing of a human with a domesticated animal for therapeutic purposes. A number of diverse studies have found that HAI can have positive effects on emotional and physical functioning, stress reactivity, and social functioning [16–18]; and among those with psychiatric symptoms, HAI interventions have been found to improve depression, anxiety, and PTSD [16, 19, 20]. Although promising, the HAI literature is tempered by methodological limitations, such as difficult-to-replicate study procedures, over-reliance on self-report measures, and lack of adequate controls/randomization (e.g., [18–20]).

Proactive targeting of emotional-numbing symptoms in the early stages of PTSD treatment can potentially improve treatment engagement and retention. Consistent with this rationale, we propose to test the efficacy of an HAI adjunct to PE for decreasing emotional-numbing symptoms and improving treatment engagement and outcomes. HAI is a compelling adjunct for PTSD EBTs due to its potential impact on patient-level outcomes as well as its viability for wide-scale implementation and dissemination.

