### Study aims

RESCUE + PE will decrease emotional-numbing symptoms of PTSD relative to the PE control arm (CI + PE) primary outcomeRESCUE+PE will be feasible and acceptable to veteransTreatment engagement will be higher for the RESCUE + PE group relative to CI + PE group (i.e., higher treatment attendance rates (primary), homework completion rates, and treatment completion rates)Treatment recovery rates (as measured by PTSD diagnostic status yes/no; decreased PTSD symptom severity; and increased quality of life) will be higher for the RESCUE + PE group compared to the CI + PE group at post treatment and at 3-month follow-upParticipants randomized to RESCUE + PE will experience a decrease in PTSD numbing from pre to post treatment relative to those randomized to CI + PI

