## Methods/design

### Participant recruitment

Seventy male and female veterans with PTSD are being recruited from a VAMC in the Southeastern United States. Veterans are referred to the study through the PTSD Clinical Team (PCT), general referrals from other VA clinics, posted flyers in approved community locations where veterans are likely to congregate, and word of mouth from other participants or individual providers.

All veterans complete an intake assessment by the PCT prior to study entry. Study staff then follow up with the intake evaluator regarding the outcome of the assessment and whether or not the veteran expressed an interest in being contacted about future opportunities to participate in research. Veterans who appear to meet the criteria for entry into the study (i.e., positive for PTSD, express willingness to engage in EBT for PTSD) and agree to be contacted are telephoned by a study staff member and given a description of the study. If interested in participating, veterans are scheduled for a telephone baseline assessment that includes informed consent. Veterans who live locally and prefer to be seen in person have the option of completing the informed consent procedures and baseline assessment appointment in the PCT clinic. Veterans who receive care via telehealth or prefer to receive their care via telehealth are mailed a consent form and baseline packet prior to their baseline assessment date so that they have a physical copy of the consent to refer to while going over the consent form with a study staff member by telephone. Following the telephone consenting/baseline appointment, participants are asked to mail the signed consent back to the research team using a self-addressed envelope. Once the signed consent form is received and the baseline measures are completed, the veteran is considered eligible for the study.

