### Sample size calculation and power analyses

For the continuous longitudinal clinical, functional, and process outcomes for Primary Aims, with 35 subjects randomized to each intervention group, we will have 85% power to detect at least a 0.3 standardized (sd units) effect size between the two intervention groups assuming three time points, and an intra-class correlation no greater than 0.5; level of significance ≤ 0.05, two-tailed. A standardized effect size of 0.35 sd (Cohen’s *d*, “small” effect) is equivalent to a raw effect size of 2.8 raw scale units for the PCL (assuming pooled sd for post-treatment PCL scores is 8.1, from preliminary data). All participants randomized to condition and having completed a baseline assessment will be included in ITT analyses.

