### Treatment effects

Treatment effects will be examined via changes on continuous measures of PTSD numbing symptoms from the CAPS-5, PCL-5, and ERNS as well as by changes on continuous CAPS-5 and PCL-5 total scores, other associated mental health outcomes (e.g., BAI, PHQ-9), and functional status/quality of life (e.g., WHODAS-II; QLI). CAPS-5 and PCL-5 emotional-numbing items will be analyzed separately based on factor analytic findings and the current hypothesis that RESCUE will specifically decrease emotional-numbing symptoms.

To evaluate pre-post treatment continuous outcome measures, HLM/mixed models will be estimated with randomized group entered as a level-2 fixed effect. Effect sizes and 95% confidence intervals will be employed in a manner consistent with accepted norms [35]. For multiple point measurement related to self-report measures, estimates of slope will also be tested. For dichotomous outcomes, rates will be assessed by chi-square comparison of between-group percentages. Diagnostic improvements will be examined by computing the percentage of treated participants who no longer meet PTSD criteria at each follow-up. Outcomes will also be evaluated using CGI-I scores at all post-treatment follow-ups (i.e., percentage of veterans receiving a CGI-I rating of 1 or 2).

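### Treatment completion is tested by an unadjusted chi-square and no covariate is named for attendance, although baseline numbing, the protocol's own predictor of engagement, is measured before randomisation

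*Protocol article*

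**What the plan says.** Study aims lists the engagement outcomes as "higher treatment attendance rates (primary), homework completion rates, and treatment completion rates". Treatment effects sets the test for yes/no outcomes: "For dichotomous outcomes, rates will be assessed by chi-square comparison of between-group percentages". Treatment completion falls most naturally under that rule. For continuous pre-post outcomes the same section says "HLM/mixed models will be estimated with randomized group entered as a level-2 fixed effect" and names no other term. Analytic strategy points to mixed models for primary and secondary outcomes in general, but no section gives attendance a method of its own.

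Background says that numbing symptoms can limit a patient's "ability and willingness to engage in treatment [10, 11], particularly a treatment that encourages connecting emotionally with trauma-related material". Study overview and Discussion repeat the idea that numbing stands in the way of engagement and retention.

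Assessment measures puts the CAPS-5, PCL-5 and the numbing scale in the baseline battery. Participant recruitment and Randomization procedures together place that battery before eligibility, and eligibility before randomisation. Analytic strategy also plans a between-group comparison of baseline psychometric variables, but attaches no consequence to it.

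**The concern.** The trial is built on the idea that numbing drives engagement. On that idea, baseline numbing predicts attendance and completion whichever arm a veteran is in. It is recorded before randomisation, so it can be used at no cost in data. Completion and attendance have no pre-treatment value of their own, so a pre-post model cannot supply a baseline adjustment for them.

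The stated completion test leaves this information out. Two things are lost. Variation that numbing could explain stays in the error term. And if one arm happens to start with more numbing, the raw contrast carries that difference. The planned baseline comparison, with no rule attached, also leaves room for a covariate to be chosen after an imbalance has been seen.

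**Working it through.** **The plan's own figure.** The only power statement is "with 35 subjects randomized to each intervention group, we will have 85% power to detect at least a 0.3 standardized (sd units) effect size", "assuming three time points, and an intra-class correlation no greater than 0.5", "level of significance ≤ 0.05, two-tailed". It concerns continuous longitudinal outcomes. Read as a difference in SD units, the standard error is sqrt((2/35) × (1 + 2×0.5)/3) = 0.195. Then 0.3/0.195 = 1.54, and power is Φ(1.54 − 1.96) = 34%, not 85%. That is a separate matter and nothing below uses it. No power is stated for attendance or completion.

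**Inputs.** From the documents: 35 per arm, 1:1 allocation, two-sided 0.05. Assumed, because the documents do not give them:
- a correlation r between baseline numbing and attendance of 0.2 to 0.5;
- an odds ratio for completion of 1.6 to 3 per SD of numbing;
- an attendance effect of 0.5 SD;
- completion of 64% v 84%. The 64% is one minus the 36% pooled dropout cited in Background; the 84% is illustrative.

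**Chance imbalance.** The SD of the between-arm difference in baseline numbing is sqrt(2/35) = 0.239 SD. So P(|difference| > 0.3) = 2 × [1 − Φ(0.3/0.239)] = 21%, and P(|difference| > 0.5) = 3.6%.

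**What an imbalance does to the raw attendance contrast.** Given an imbalance b, the contrast shifts by r × b. The test statistic then has mean r × b/0.239 and variance 1 − r². Under no treatment effect:

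| r | shift at b = 0.5 | two-sided error at b = 0.25 | two-sided error at b = 0.5 |
|---|---|---|---|
| 0.2 | 0.10 SD | 5.0% | 6.5% |
| 0.3 | 0.15 SD | 5.1% | 8.5% |
| 0.5 | 0.25 SD | 5.1% | 14.6% |

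Over all randomisations the error remains 5%, because the cases with little imbalance fall below it (for example 4.0% at r = 0.3 with none).

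**Precision for attendance.** Adjustment reduces the residual SD to sqrt(1 − r²). Power is approximately Φ(0.5/[0.239 × sqrt(1 − r²)] − 1.96):
- unadjusted: 55%;
- r = 0.2: 57%;
- r = 0.3: 59%;
- r = 0.5: 68%.

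**Completion, by simulation.** With 64% in both arms, the chi-square rejects in 5.0% to 5.3% of trials whatever the odds ratio (1 to 3). Among trials with an imbalance of 0.4 to 0.6 SD it rejects in 6.6%, 7.2% and 11.5% at odds ratios of 1.5, 2 and 3, and the completion difference shifts by about 5, 7 and 10 points.

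With 64% v 84%, the chi-square has about 48% power. An unadjusted likelihood-ratio test already has about 50%, so 2 to 3 points come from the change of test and not from adjustment. Compared with that test, adjusting for numbing adds about 1 point at an odds ratio of 1.6, 2.5 points at 2 and 7 points at 3. Null error stays at 5% to 6%.

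**Model size.** Under these rates the expected number of non-completers is 35 × 0.36 + 35 × 0.16 = 18.2, so about 18.

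**The case against.** The strongest reply is that covariate lists are commonly left to an analysis plan that is not shown, and that naming randomised group as a level-2 effect does not say it is the only term. That stands for the mixed models and for the silence on strata. It does not cover completion, because the chi-square rule is a stated method.

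A reader might also infer more than the text supports:
- **That attendance is compared as a raw figure.** The article does not say so. An attendance rate is not dichotomous, and Analytic strategy points to mixed models. What can be said is that its method is unassigned and no covariate is named.
- **That imbalance can mimic an engagement effect in general.** It cannot in that sense. A randomised test already allows for chance imbalance, and its overall error is about 5%. The distortion is conditional on a sizeable imbalance and matters only if numbing is fairly strongly related to engagement.
- **That the shift should be judged against 0.3 SD.** That figure belongs to the longitudinal outcomes; attendance has no stated target.
- **That telehealth or in-person care should be a covariate or stratum.** Participant recruitment mentions telehealth to explain how consent and baseline papers are sent. No section says that care mode predicts engagement.

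It is also fair that the link between numbing and engagement is asserted without a figure, and that a sample made up entirely of veterans with PTSD may have a narrow range of numbing. Both would push the gain towards the low end.

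**Conclusion.** The point holds as a modest, inexpensive improvement to a stated method. It is not a validity failure. The article fixes an unadjusted test for completion and leaves attendance without a method or covariate, while its own rationale identifies a predictor that is in hand before randomisation.

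The gain is small if the link is weak: about 2 power points for attendance at r = 0.2 and about 1 for completion at an odds ratio of 1.6. It is worthwhile if the link is as strong as the rationale implies: about 12 points at r = 0.5 and about 7 at an odds ratio of 3. These figures rest on the assumed correlations, odds ratios, attendance effect and completion rates. What does not depend on them is the chance of imbalance itself, and the value of fixing the covariate before any imbalance is seen.

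**What to change.** In Treatment effects, analyse treatment completion by logistic regression on arm and one prespecified baseline CAPS-5 numbing score, with the items that form it named in advance. Report the result as a standardised risk difference with a 95% confidence interval, so that readers do not have to interpret a conditional odds ratio. Keep the chi-square as a supporting table. State the model for attendance and include the same score. Say that covariates will not be selected on observed baseline imbalance.

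The cost is two or three sentences, with no new data and no change to allocation. The one downside is sparse events: with about 18 non-completers expected under the assumed rates, the completion model should stay at these two terms.

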### Study overview

The current study is a DoD-sponsored project (W81XWH-15-1-0087) designed to develop and pilot test the feasibility, acceptability, and efficacy of an adjunctive intervention for increasing treatment compliance with EBTs for PTSD by targeting the emotional-numbing symptoms of PTSD. RESCUE, *Recovery through Engagement with Shelter Canines, Understanding, and Exposure*, is a HAI intervention that was developed during the initial stages of the project as an adjunct to Prolonged Exposure for PTSD (PE). The innovative study design focuses on increasing PTSD treatment engagement through HAI designed to target the emotional-numbing symptoms of PTSD which are theorized to impede treatment compliance and retention. Although the current trial focuses on veterans treated at a Veterans Affairs Medical Center (VAMC), the study design and findings will have significant relevance for the broader population of individuals with PTSD across diverse treatment settings.

Feasibility, acceptability, and initial efficacy testing of the experimental treatment condition is being conducted using a randomized controlled trial (RCT) of 70 veterans with PTSD assigned to receive either RESCUE paired with PE (RESCUE + PE) or community involvement paired with PE (CI + PE). Consistent with the manual guidelines [21], PE consists of up to 12 weekly sessions. Veterans are encouraged to engage in their assigned volunteer activity (either volunteering at the animal shelter or engaging with a community agency, depending on condition) a minimum of once per week. In addition to the baseline assessment, veterans are assessed at mid-treatment (session 5), immediately post treatment (12 weeks), and at the 3-month follow-up (see Fig. 1 below). Clinical outcomes include levels of PTSD, depression, anxiety, and functional status/quality of life. Additionally, after completing treatment, veterans are asked to participate in an individual thematic interview to get their impression of the treatment program overall, their perceptions regarding their current functioning and symptoms relative to the start of treatment, any difficulties/barriers they faced with aspects of the program, and their thoughts about specific components of PE (i.e., imaginal and in vivo) and their volunteer assignment.

**Fig. 1 Fig1:**
[figure not shown]
Consolidated Standards of Reporting Trials (CONSORT) Diagram

### Study aims

RESCUE + PE will decrease emotional-numbing symptoms of PTSD relative to the PE control arm (CI + PE) primary outcomeRESCUE+PE will be feasible and acceptable to veteransTreatment engagement will be higher for the RESCUE + PE group relative to CI + PE group (i.e., higher treatment attendance rates (primary), homework completion rates, and treatment completion rates)Treatment recovery rates (as measured by PTSD diagnostic status yes/no; decreased PTSD symptom severity; and increased quality of life) will be higher for the RESCUE + PE group compared to the CI + PE group at post treatment and at 3-month follow-upParticipants randomized to RESCUE + PE will experience a decrease in PTSD numbing from pre to post treatment relative to those randomized to CI + PI

## Methods/design

### Participant recruitment

Seventy male and female veterans with PTSD are being recruited from a VAMC in the Southeastern United States. Veterans are referred to the study through the PTSD Clinical Team (PCT), general referrals from other VA clinics, posted flyers in approved community locations where veterans are likely to congregate, and word of mouth from other participants or individual providers.

All veterans complete an intake assessment by the PCT prior to study entry. Study staff then follow up with the intake evaluator regarding the outcome of the assessment and whether or not the veteran expressed an interest in being contacted about future opportunities to participate in research. Veterans who appear to meet the criteria for entry into the study (i.e., positive for PTSD, express willingness to engage in EBT for PTSD) and agree to be contacted are telephoned by a study staff member and given a description of the study. If interested in participating, veterans are scheduled for a telephone baseline assessment that includes informed consent. Veterans who live locally and prefer to be seen in person have the option of completing the informed consent procedures and baseline assessment appointment in the PCT clinic. Veterans who receive care via telehealth or prefer to receive their care via telehealth are mailed a consent form and baseline packet prior to their baseline assessment date so that they have a physical copy of the consent to refer to while going over the consent form with a study staff member by telephone. Following the telephone consenting/baseline appointment, participants are asked to mail the signed consent back to the research team using a self-addressed envelope. Once the signed consent form is received and the baseline measures are completed, the veteran is considered eligible for the study.

### Randomization procedures

Once eligibility is established, veterans are assigned 1:1 to one of the two treatment groups by the Project Coordinator using a web-based computer-generated randomization scheme. Once a veteran is randomized and attends the first session, they are entered into the study and included in the intent-to-treat (ITT) analysis. The post-treatment assessors (12- and 3-month assessors) will be blinded to condition. The Principal Investigator (PI) (for clinical oversight/supervision) and Project Coordinator (for randomization/regulatory reasons) will not be blinded to treatment condition. The study therapists likewise will not be blinded because discussion of volunteer assignments is part of the treatment protocol. It is not anticipated that the post-treatment assessors will need to be unblinded as this will be their only point of contact with the study participant. If the blind is accidentally broken, the Clinician Administered PTSD Scale (described below) will be reviewed by another team member for fidelity and evaluated against the PTSD Symptom Checklist (described below) which is self-report.

Inclusion criteria for the study are as follows: (1) *Diagnostic and Statistical Manual for Mental Disorders, version 5* (DSM-V) PTSD diagnosis (via the Clinician Administered PTSD Scale; CAPS [22];) stemming from a duty-related Criterion A event [23]; (2) male or female aged 18 to 64 years.

Exclusion criteria for the study are as follows: (1) presence of an active substance-use disorder that requires medical detoxification; (2) diagnosis of Antisocial Personality Disorder or history of animal cruelty; (3) presence of delirium, dementia, amnestic disorders, or other cognitive disorders and psychotic disorders that would likely interfere with the ability to consent or comply with study procedures; (4) presence of active/uncontrolled bipolar I or II disorder; (5) current use of benzodiazepine medications (if willing, participants are required to taper and cease use under physician supervision, and they must be off the medication(s) for at least 2 weeks prior to enrolling in the study); (6) recent prescription of an SSRI antidepressant medication or a recent change in dosing (participants must be on a consistent dose for at least 2 weeks prior to enrollment and throughout the study); (7) suicidal or homicidal ideation with intent; (8) lack of English language fluency; and (9) presence of a specific phobia related to dogs or any other relevant aversion to dogs (i.e., allergy). Once enrolled, participants will only be discontinued from the study if the study appears to be causing them undue or atypical distress and/or if the patient elects to terminate their study participation.

See description of instruments below under the “Assessment measures” section and Fig. 2 for the study assessments and procedures.

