#### Recovery through Engagement with Shelter Canines, Understanding, and Exposure (RESCUE)

Half of all veterans are randomly assigned to receive RESCUE concomitant with PE. RESCUE volunteer sessions occur once weekly at an area Society for the Prevention of Cruelty to Animals (SPCA) chosen by the veteran and last approximately 90 min. Expectations regarding volunteer assignments are reviewed by study staff prior to the start of treatment and progress or difficulties with the assignments are discussed throughout treatment as described above. Prior to starting their volunteer assignment, participants receive an orientation by SPCA professionals consistent with what is provided to community volunteers. This training includes an orientation to the physical space of the shelter, basic safety and handling education, and discussion of daily tasks involving interaction with the canines that can be accomplished. Participants are limited to working with *non-aggressive* dogs.

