### Analytic strategy

Data screening for violations of proposed statistical methods assumptions (normality of endogenous variables, linear relations among variables, no outliers, limited missing data/appropriate method for handling missing data) will include histograms, bivariate correlations, Q-Q plots, and other diagnostic methods. Processes associated with subject attrition will be examined to determine whether a missing-at-random assumption is defensible. Data will be analyzed to determine whether missing values are correlated with any baseline values and all relevant psychometric variables will be examined between groups at the baseline point of measurement to ensure adequate randomization. Given limitations of last-observation-carried-forward (LOCF), hierarchical linear models (HLM)/mixed models will be used for ITT analyses of primary and secondary outcome variables. Statistically significant treatment-related changes will be qualified with effect-size estimation and 95% confidence interval estimation.

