## Discussion

Despite systemic efforts by the DoD and VA to ensure that EBTs are available to all veterans with PTSD, many veterans are not initiating or completing treatment. This is a significant issue given that PTSD does not typically remit over time and is associated with significant impairment across a range of psychosocial indices. Given the increased availability of EBTs, and the well documented and robust effect sizes for patients who complete PE, more attention should be given to testing novel methods for improving treatment engagement and retention rather than further improving outcomes among those who comply with PE treatment guidelines. As with other psychiatric disorders (e.g., depression), the symptoms that pose as a barrier to treatment engagement should be targeted directly to improve treatment initiation, engagement, and completion [36]. In this effort, the current clinical trial focuses on addressing the emotionally numbing symptoms of PTSD using a HAI model.

In addition to being part of the symptom profile of PTSD, emotional numbing can serve as a barrier to care through its heightened association with apathy, low motivation, and feeling disconnected from others [10, 14]. Unfortunately, current EBTs do not target emotional numbing directly. Thus, although emotional-numbing symptoms can decrease with treatment of a sufficient duration, targeting them proactively and effectively in the early stages of treatment is likely to improve overall treatment retention and subsequent clinical improvement. Based on the broader HAI literature, RESCUE (the experimental condition) was designed explicitly as an adjunctive therapy to augment extant EBTs by decreasing emotional-numbing symptoms, increasing veteran “buy in,” facilitating avenues for effective EBT psycho-education, and increasing supportive and therapeutic in-vivo exposure and commensurate behavioral activation, thereby improving PTSD EBT engagement and completion rates.

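### The ITT set is defined in two contradictory ways, and the version that requires session 1 attendance removes non-starters from the attendance and completion comparisons

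*Protocol article*

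**What the plan says.** Two sections of the protocol article state who is in the ITT analysis.

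- Randomization procedures: "Once a veteran is randomized and attends the first session, they are entered into the study and included in the intent-to-treat (ITT) analysis".
- Sample size calculation and power analyses: "All participants randomized to condition and having completed a baseline assessment will be included in ITT analyses".

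Neither sentence refers to the other, and no other section chooses between them.

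The order of events is given elsewhere. Participant recruitment says "Once the signed consent form is received and the baseline measures are completed, the veteran is considered eligible for the study", and Randomization procedures continues "Once eligibility is established, veterans are assigned 1:1 to one of the two treatment groups". Analytic strategy says that "hierarchical linear models (HLM)/mixed models will be used for ITT analyses of primary and secondary outcome variables", so the choice of set governs the main results.

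Study aims names emotional numbing as the primary outcome. Under the engagement aim it expects "higher treatment attendance rates (primary), homework completion rates, and treatment completion rates" in the RESCUE + PE arm. The Discussion includes starting treatment in the rationale: "the symptoms that pose as a barrier to treatment engagement should be targeted directly to improve treatment initiation, engagement, and completion".

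**The concern.** Attending session 1 happens after randomisation. A set that requires it is a modified ITT set, whatever it is called. Whether a veteran turns up may depend on the assigned arm. In the RESCUE section, "Expectations regarding volunteer assignments are reviewed by study staff prior to the start of treatment", so a veteran in that arm can learn what is asked and decide not to begin. In the control arm, veterans have to arrange their own agency placement.

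The exclusion matters most where it overlaps with the outcome. A veteran who never attends has a known value without any assessment: zero sessions, and not a completer. Removing these veterans conditions the attendance comparison on attendance.

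Leaving both definitions in force also allows the set to be chosen after data have been seen. The principal investigator and the project coordinator are unblinded and, under Data management, have access to the interim and final dataset.

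**Working it through.** **Step 1: what separates the two sets.** Baseline measures must be complete before a veteran is eligible, and randomisation follows eligibility. Every randomised veteran therefore has a baseline, and the sample-size-section rule means all randomised. The Randomization procedures rule adds attendance at session 1. The sets differ by the randomised veterans who never attend session 1, and by nobody else.

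**Step 2: effect on mean sessions attended.** The documents give no figure to reproduce here, because no rate of missing session 1 is stated. Let p be the proportion not starting and m the mean sessions among starters, with subscripts R (RESCUE + PE) and C (CI + PE).

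- All randomised, non-starters scored 0: difference = (1 − p_R)·m_R − (1 − p_C)·m_C
- Session-1 set: difference = m_R − m_C
- Part the session-1 set cannot show: p_C·m_C − p_R·m_R

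The inputs are 35 randomised per arm (sample size section), m_R = m_C = 8 of up to 12 sessions (assumed), and the non-start rates below (assumed).

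| Non-start, RESCUE vs CI | Non-starters of 70 | All-randomised means | Difference | Session-1 set |
|---|---|---|---|---|
| 10% vs 10% | 3.5 + 3.5 = 7 | 0.90×8 = 7.2 vs 7.2 | 0 | 0 |
| 5% vs 10% | 1.75 + 3.5 = 5.25 | 0.95×8 = 7.6 vs 7.2 | +0.4 | 0 |
| 15% vs 25% | 5.25 + 8.75 = 14 | 0.85×8 = 6.8 vs 0.75×8 = 6.0 | +0.8 | 0 |
| 25% vs 15% | 8.75 + 5.25 = 14 | 6.0 vs 6.8 | −0.8 | 0 |

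The zeros in the last column follow from assuming equal means among starters. They isolate what the rule hides, and do not predict the trial's result.

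**Step 3: effect on treatment completion.** Assume 64% completion among starters in both arms. With non-start of 10% in RESCUE and 20% in CI, all-randomised completion is 0.90×64% = 57.6% against 0.80×64% = 51.2%, a difference of 6.4 percentage points. Swapping the rates gives −6.4 points. The session-1 set shows 0 both times.

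**Step 4: effect on symptom and quality-of-life outcomes.** These are analysed by mixed models. A non-starter with only a baseline value adds almost nothing to the estimated difference in change between arms. The two sets therefore give nearly the same estimate unless non-starters attend later assessments.

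**The case against.** The strongest defence is that the Randomization procedures sentence gives a sufficient condition and not a necessary one. That reading is weak, because the same sentence makes session 1 the point at which a veteran enters the study. If it was intended, the sentence still needs rewriting.

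A second defence is that non-starters may be few. Participant recruitment selects veterans who say they are willing to have an evidence-based treatment, and the documents support no particular rate. This stands: the size is unknown, and the table is only a range of assumptions.

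A reader might also infer four stronger points, which the documents do not support.

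- **That every outcome is materially distorted.** The session-1 rule departs from ITT for all of them, but Step 4 shows that the practical effect on mixed-model outcomes is small when non-starters have baseline data only. Emotional numbing, the named primary outcome, is among these.
- **That non-starters are denied the 12-week and 3-month assessments.** No section says so. Assessment measures encourages veterans who drop out of treatment to complete follow-up and is silent on those who never start. The participant flow diagram and assessment schedule are not shown, so they cannot settle it.
- **That both arms are told what is expected before treatment.** This is stated for RESCUE only. Arm-dependent non-starting is plausible but not documented.
- **That the rule works for or against RESCUE.** The direction cannot be known; reversing the assumed rates reverses the sign of what is hidden.

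**Conclusion.** The contradiction is real and lies within the article, so it is not a detail left to an analysis plan. The session-1 version is the wrong rule for something called ITT. Its clear harm is confined to the engagement aim: attendance, labelled primary there, and treatment completion. For those outcomes, no benefit or harm arising between randomisation and session 1 can be seen.

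With 8 sessions on average among starters in both arms, the hidden difference is 0 at equal non-start rates, 0.4 sessions at 5% versus 10%, and 0.8 sessions in either direction at 15% versus 25%. These sizes rest wholly on assumed rates. The finding that the two definitions conflict rests on none of them.

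**What to change.** - In Randomization procedures, delete the condition of attending session 1. Use the all-randomised set from the sample size section for every ITT analysis.
- Score non-starters as 0 sessions attended and as non-completers, and report their number by arm.
- State that the invitation to follow-up assessments given to veterans who drop out also covers non-starters still within their assessment windows.
- If a set of session-1 starters is kept, label it modified ITT and use it only as a sensitivity analysis.

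The text change is small. The added cost is assessor time and payments of US$50 at each of two assessments: 3.5 × 2 × 50 = US$350 if 5% of 70 do not start, and 14 × 2 × 50 = US$1,400 if 20% do not (both rates assumed). The trial is ongoing, so some non-starters may already be past their windows. Their attendance and completion can still be scored, but their symptom outcomes would remain missing.
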